### Data analysis

The cohort-specific characteristics of the recruited participants will be described by exploratory data analysis. Normally distributed variables will be summarized as mean and standard deviation, whereas, median and inter-quartile range will be used for the variables following skewed distributions. Binary and categorical variables will be presented as counts and percentages. Appropriate statistical tests (Student’s t-tests, Pearson chi-square tests, and Mann-Whitney test) will be used to detect the differences in baseline characteristics of the two intervention groups. A probability of < 0.05 will be considered statistically significant. The correlation between the confounders and outcome will be evaluated using Pearson or Spearman correlation, whichever is appropriate. Multi-collinearity between the predictor variables will be assessed using variance inflation factor (VIF), and a predefined cut-off of 2 will indicate the absence of multi-collinearity.

#### Modeling the clinical effectiveness of the intervention

A linear mixed effects model—a statistical technique for analyzing longitudinal data—will be employed to assess the impact of the intervention on the outcomes described above. The model for continuous outcome variables is specified as:

$$Yi=Xi\beta+Zibi+\varepsilon i,$$

where Yi represents the vector of responses for each subject across multiple follow-up time points. Xi denotes the matrix of fixed effects (such as treatment, baseline covariates, and general time trends) with associated regression coefficients β. Zi represents the matrix of random effects accounting for subject-specific trends (e.g., morbidity, adherence to the intervention), with corresponding random effect coefficients bi, and εi denotes the vector of residual errors. Both intention-to-treat and per-protocol analyses will be conducted.

#### Modeling the changes in centiles of anthropometry curves

Percentage changes in weight and BMI will be calculated by subtracting baseline values from follow-up measurements, dividing the difference by the baseline value, and then multiplying by 100. Generalized linear mixed-effects models (GLMMs) will be used to model the percent changes of indices. GLMMs will estimate the probability of improvement in the BMI and weight in the intervention group from baseline in comparison to the control group, after adjusting for all the other possible covariates.

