### Methods and analysis

This is a community-based intervention study where participants will be enrolled in two cohorts: undernourished pregnant (BMI < 18.5 kg/m^2^; 18–35 years, *n* = 60) and undernourished non-pregnant ((BMI < 18.5 kg/m^2^; 18–35 years, *n* = 60) women from Bauniabadh and adjacent slum areas of Mirpur, Dhaka. For comparison, well-nourished pregnant women (BMI 20–24.9 kg/m^2^; 18–35 years, *n* = 30), who will be screened through household surveys from the Bauniabadh and adjacent slum area of Mirpur, Dhaka, and well-nourished non-pregnant (BMI 20–24.9 kg/m^2^; 18–35 years, *n* = 30) women of reproductive age will be recruited. We will use two specific aims, AIM 1 A and AIM 1B. In AIM 1 A, we will compare the small intestinal (SI) and fecal microbiota and the plasma, duodenal, and fecal proteomes/metabolomes of the undernourished non-pregnant cohort with histopathologic evidence of EED with the well-nourished non-pregnant cohort with no histopathologic evidence of EED undergoing routine endoscopic evaluation for dyspepsia. Upper gastro-intestinal (UGI) endoscopy will be performed on non-pregnant women and biopsy samples will be collected for diagnosis of EED and histopathological scoring. In AIM 1B, we will perform an intervention study. After UGI endoscopy, undernourished non-pregnant cohort will be randomized into two groups (*n* = 30/arm) and receive daily dietary supplementation with either shelf-stable microbiota-directed balanced energy protein (MD-BEP) or ready-to -use supplementary food balanced energy protein (RUSF-BEP) for 90 days. After cessation of the intervention they will be further followed up for another 270 days and biological samples will be collected at scheduled time points. The well-nourished non-pregnant cohort will not receive any nutritional intervention will serve as a reference control group. The undernourished pregnant cohort will also be randomly (*n* = 30/arm) assigned to receive either MD-BEP or RUSF-BEP daily for 6 months until the child birth and thereafter for 3 months and followed up for another 9 months. During this period anthropometry will be measured and biological samples including fecal and plasma samples will be collected from the mothers and their infants in scheduled time points. The well-nourished pregnant cohort will not be supplemented with MD-BEF or RUSF-BEP but will be followed-up with anthropometric measurement and sample collection like undernourished pregnant cohort. Due to ethical concerns related to performing endoscopy in pregnant women, UGI endoscopy in pregnant women will not be performed. Anthropometric, socio-demographic, and laboratory assay data will be compared across study groups. Additionally, potential EED biomarkers will be evaluated for correlations with nutritional status and histopathological findings, alongside analyses of the microbial community structure. Prior to participation, each subject will receive a comprehensive explanation of the study and provide written informed consent. Participants capable of signing will do so, while those unable to sign will provide a thumb impression as an alternative. A separate consent form specific to endoscopy and supplemental interventions will be administered, following the same consent procedure. The endoscopy consent form thoroughly details all aspects of the procedure, including associated risks, ensuring complete transparency. No information pertinent to the participant’s understanding is withheld. While enrolling the neonates, a signed written informed consent from the parents or guardians is obtained. All consents are obtained and documented in presence of the study physician at the study field office in front of a witness, who also sign the document as the witness. This study was conducted and reported in accordance with the CONSORT guidelines. The first participant was enrolled on 28 April 2023. Estimated end date is 31 December 2026. The schedule of study events is presented in Fig. 1.

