### AIM 1A: non-pregnant cohort

In AIM 1 A, for the healthy group, we plan to recruit a cohort of well-nourished Bangladeshi women who will undergo esophagogastroduodenoscopy (EGD) for evaluation of functional dyspepsia and identify 30 well-nourished participants who have normal duodenal mucosal histology. Healthy women (BMI 20–24.9 kg/m^2^) of childbearing age who have been referred for evaluation of functional dyspepsia as defined by Rome IV criteria, will be enrolled from women attending the Gastroenterology OPD of Bangladesh Specialized Hospital (BSH), Dhaka, Bangladesh, and also from the community who meet the inclusion criteria. Duodenal biopsies, duodenal aspirates, plasma and fecal specimens from these participants at the time of endoscopy and serial plasma and fecal samples will be collected according to the follow-up schedule (Fig. 3). These women will be considered as the control group for the non-pregnant cohort and will be followed for 360 days but will not receive any nutritional intervention. Undernourished (< 18.5 kg/m^2^; 18–35 years) women of childbearing age will be enrolled from Bauniabadh and adjacent slum areas of Mirpur, Dhaka, and EGD will be performed among 60 women at icddr, b Dhaka Hospital, or BSH, Dhaka. Participants will be screened through household surveys from the Bauniabadh and adjacent slum area of Mirpur, Dhaka. After EGD, the undernourished women will be randomized into two groups (*n* = 30/arm) and receive daily dietary supplementation with either MD-BEP or RUSF-BEP for a period of 90 days, with a further 270 days of follow-up after cessation of the intervention, and biological samples will be collected from the participants according to the schedule. The EGD scheme is presented in Fig. 2.

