### AIM 1B: pregnant cohort

For AIM 1B, beginning at the end of the first trimester, undernourished (< 18.5 kg/m^2^) pregnant women (aged 18–35 years) will be randomly assigned to receive either MD-BEP or RUSF-BEP for the duration of their pregnancy and during the first three postnatal months, in addition to standard antenatal care (*n* = 30/arm). A parallel cohort of age-matched well-nourished pregnant women (*n* = 30) who will not receive any nutritional intervention will serve as a reference control group. Due to safety, sensitivity, and ethical concerns related to performing endoscopy in pregnant women, EGD will not be performed on these women. The women will receive standard antenatal care, will be followed up and serial plasma and fecal samples will be collected according to Fig. 1. These women will be considered as the control group for the pregnant cohort and will not receive any nutritional intervention.

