#### Ready-to-use supplementary food- balanced energy protein (RUSF-BEP)

Women in the RUSF-BEP group will receive a single serving of RUSF-BEP daily, similar to the MD-BEP arm. The feeding will initially in the field office for at least one week, and continued at home afterwards. The feeding will be supervised by the respective FRAs. Each serving of RUSF-BEP will also provide approximately 500 Kcal, 14 g of protein, and necessary micronutrients following the recommendations from the expert panel convened by the BMGF on nutritional supplementation in pregnancy [15].

The amount in each serving of the supplements and the compositions are shown in Tables 1 and 2, respectively, which are in conformity with the recommendations from the expert panel convened by the BMGF on nutritional supplementation in pregnancy [15].

**Table 1 Tab1:** Ingredients used in MD-BEP and RUSF-BEP formulations with amount per serving

Ingredients	MD-BEP (gms)	RUSF-BEP (gms)
Chickpea, flour	14.00	-
Soy flour	18.50	-
Peanut, paste	14.25	-
Green banana powder	12.50	-
Sugar, powder	11.90	10.30
Soybean Oil	20.00	28.50
Micronutrient Premix	2.30	2.30
Amino acid powder (Lysine 0.15, Methionine 0.05, Cysteine 0.05)	0.25	-
Stabilizers (Lecithin)	0.30	0.30
Rice, flour	-	13.40
Lentil, flour	-	14.60
Skimmed Milk, Powder	-	27.60
Total	94	97

Enrolled women will be closely monitored by Field Research Assistants for one week to identify any potential side effects or adverse events (e.g., rash, urticaria due to food allergy, or notable changes in clinical status). Any such events will be managed in accordance with the standard of care. Study participants will be given dietary counseling focused on promoting dietary diversity, incorporating vegetable oil into cooked meals as an energy source, and encouraging regular consumption of animal-based foods such as small fish or chicken, alongside a consistent intake of vegetables. The study participants will also receive support for any intercurrent illnesses detected by the study team as well as proper referral will be provided.

**Table 2 Tab2:** Nutritional composition of MD-BEP and RUSF-BEP

Nutritional composition	BEP recommendation	MD-BEP (per 94 g)	RUSF-BEP (per 97 g)
Total Energy(kcal)	250–500	494.62	497.54
Protein (g)	14–18	14.18	14.33
Energy from Added Sugar, (% of total energy)	< 10%	9.36%	8.05%
Energy from Fat (FER), (% of total energy)	10–60%	58.48%	53.08%
Total ω−3 (g)	≥ 1.30	1.70	2.01
(ω−6/ω−3) ratio	5–10:1	8.29:1	7.34:1

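### The weight and BMI improvement model names "the control group" as comparator, a label the protocol reserves for unsupplemented, non-randomised well-nourished women; the contrast should be MD-BEP versus RUSF-BEP

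*Protocol article*

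**What the plan says.** The section *Modeling the changes in centiles of anthropometry curves* defines percent change in weight and BMI from baseline. It then says that "GLMMs will estimate the probability of improvement in the BMI and weight in the intervention group from baseline in comparison to the control group", with adjustment for other covariates. It does not say who is in either group.

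The label is defined elsewhere in the article:

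- *AIM 1A*, of the well-nourished women having endoscopy: "These women will be considered as the control group for the non-pregnant cohort".
- *AIM 1B*, of the well-nourished pregnant women: "These women will be considered as the control group for the pregnant cohort and will not receive any nutritional intervention".
- *Methods and analysis*: "The well-nourished non-pregnant cohort will not receive any nutritional intervention will serve as a reference control group". The abstract says the same.

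Randomisation takes place only among undernourished women, 30 per arm in each cohort. After endoscopy the non-pregnant women "receive daily dietary supplementation with either MD-BEP or RUSF-BEP for a period of 90 days". The pregnant women "will be randomly assigned to receive either MD-BEP or RUSF-BEP for the duration of their pregnancy" and for three months after birth. *Data analysis* plans tests to "detect the differences in baseline characteristics of the two intervention groups", so both randomised arms carry the intervention label.

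**The concern.** An analyst who follows the article's own vocabulary would fit this model to supplemented, undernourished women against unsupplemented, well-nourished women. Those groups were formed by BMI, not by randomisation. A favourable result would be compatible with thin women gaining weight when given extra food, with regression to the mean after selection on low BMI, or with other differences between the groups. It would not tell the reader whether the microbiota-directed product does better than a similar supplement without that design, which is the contrast that randomisation protects.

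The singular intervention group adds a second gap: it could be MD-BEP alone or both supplements pooled. Under pooling, the model would contain no comparison between the randomised arms at all.

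**Working it through.** The article gives no figure for this comparison, so there is none to reproduce. The check sets the possible comparators side by side and sizes what differs.

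**1. What differs between the groups compared**

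| | MD-BEP vs well-nourished women | MD-BEP vs RUSF-BEP |
|---|---|---|
| Randomised | No | Yes, 30 vs 30 in each cohort |
| Eligibility BMI (kg/m²) | below 18.5 vs 20–24.9 | below 18.5 in both |
| Energy from supplement (Table 2) | 494.62 − 0 = 494.62 kcal/day | 494.62 − 497.54 = −2.92 kcal/day |
| Protein from supplement (Table 2) | 14.18 − 0 = 14.18 g/day | 14.18 − 14.33 = −0.15 g/day |
| Recruitment, non-pregnant | household survey in the slum area vs hospital gastroenterology outpatients and community | same source |

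The text on the comparator product agrees with Table 2: "Each serving of RUSF-BEP will also provide approximately 500 Kcal, 14 g of protein, and necessary micronutrients".

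**2. Whether covariate adjustment helps.** Every supplemented woman enters below 18.5 and every well-nourished woman at 20 or above, which leaves a gap of 20 − 18.5 = 1.5 kg/m². No baseline BMI is represented in both groups. A model with group and baseline BMI therefore rests on extrapolation, not on women of like BMI.

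**3. The percent scale.** For the same absolute gain g, percent change is 100 × g / baseline. Take g = 0.5 kg/m² as an illustration, with baselines of 17.5 (mean BMI of the 22 women with matched samples in the earlier study described in the Introduction) and 22.45 (midpoint of 20–24.9):

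- 100 × 0.5 / 17.5 = 2.86%
- 100 × 0.5 / 22.45 = 2.23%
- ratio 22.45 / 17.5 = 1.28

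This ratio applies to the size of percent change only. Percent change and absolute change have the same sign, so the scale does not alter the probability of any gain.

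**4. Selection on BMI with no effect of anything.** Simulation for non-pregnant women: true BMI normal with mean/SD 21/3 or 23/3.5; baseline and follow-up each equal true BMI plus independent within-person variation of SD 0.2 to 0.5; low-BMI group also cut at 14. All these values are assumptions, as the article gives none.

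- Mean percent change: +0.10% to +0.73% in the low-BMI group, −0.13% to +0.05% in the normal-BMI group.
- Probability of a gain: 0.52–0.57 against 0.48–0.51.

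The tilt is modest, but it favoured the low-BMI group in every setting tried. It is not offered for the pregnant cohort, where weight gain is expected in all groups.

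**The case against.** The strongest reply is that the authors may simply have meant RUSF-BEP. The sentence sets one intervention group against one control group, which fits a two-arm trial. In the earlier feeding trial described under *Nutritional intervention*, the RUSF product was the comparator. Improvement in weight and BMI is also an odd endpoint for women selected for a normal BMI. In several places the well-nourished women are called a reference control group rather than simply the control group.

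This is plausible as to intent, but no sentence in the article says it. *AIM 1A* and *AIM 1B* use the unqualified label for the well-nourished women. If RUSF-BEP was meant, the sentence uses a defined label for a different group and still has to be corrected. Nor is this a detail left to an unseen analysis plan: the article states the comparison, with a label it has already assigned.

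Other replies limit the point, and they stand:

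- A reader might infer that the effectiveness analysis as a whole is non-randomised. The documents do not support that. The linear mixed model under *Modeling the clinical effectiveness of the intervention* has a treatment term, is planned by intention to treat and per protocol, and does not name this control group.
- A reader might infer that the percent scale inflates the probability of improvement. It does not if improvement means any gain, and the section states no percentage cut-off.
- A reader might want an odds ratio for the spurious effect of feeding. That would need an assumed gain and SD, neither of which is in the article. A scenario in which unsupplemented women average no gain would not fit pregnant women.
- Recruitment sources differ only in part, because well-nourished non-pregnant women also come from the community.
- Comparing the groups descriptively, or even testing them, is legitimate in an exploratory study. The fault lies in reading such a comparison as a treatment effect.

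**Conclusion.** The point holds for the weight and BMI improvement model. Read by the article's own definitions, its comparator is a non-randomised, unsupplemented group with a non-overlapping BMI range. If RUSF-BEP was intended, the label contradicts those definitions. Which of the two was intended cannot be settled from the article, but both call for the same correction.

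The main size is structural: against the well-nourished women the supplement contrast is the full 494.62 kcal and 14.18 g of protein a day, whereas between the randomised arms it is 2.92 kcal and 0.15 g. Only the second can separate the formulation from the extra energy. The 1.28 ratio assumes equal absolute gains at the two illustrative baselines. The simulated tilt depends on assumed BMI distributions, and only its direction should be relied on.

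**What to change.** In *Modeling the changes in centiles of anthropometry curves*, replace the two group labels by MD-BEP arm versus RUSF-BEP arm, fitted within each undernourished randomised cohort (non-pregnant and pregnant). In *AIM 1A* and *AIM 1B*, and wherever else the label occurs, call the well-nourished women a reference group. State that comparisons with them are non-randomised and are not read as a treatment effect.

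The cost is wording only: no new data, visits or participants. It can be done before analysis, as the stated end date is 31 December 2026.

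The authors should expect limited precision. With 30 per arm, two-sided alpha 0.05 (sidedness assumed), no dropout and a single continuous outcome, the difference detectable with 80% power is (1.960 + 0.842) × √(2/30) = 0.72 SD; power for 0.5 SD is about 49%. This is a reason to report the randomised contrast with a confidence interval, not a reason to prefer the confounded one.

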**Methods and analysis:**

This is a community-based intervention study where pregnant women and non-pregnant women of reproductive age (18-35 years) will be screened through household surveys from the Bauniabadh and adjacent slum area of Mirpur, Dhaka (pregnant and non-pregnant cohorts, n=90 each). Using Body Mass Index (BMI), both the groups will be categorized into undernourished (BMI <18.5kg/m2, n=60 each with pregnant and non-pregnant cohort) and well-nourished (BMI >20-24.9 kg/ m2, n=30, each with pregnant and non-pregnant cohort). Upper gastro-intestinal (UGI) endoscopy will be performed on non-pregnant women (both well-nourished and undernourished cohorts) and biopsy samples will be collected for diagnosis of environmental enteric dysfunction (EED) by histopathological scoring. We will compare the small intestinal (SI) and fecal microbiota and the plasma, duodenal, and fecal proteomes/ metabolomes of the undernourished non-pregnant cohort with histopathologic evidence of EED with the well-nourished non-pregnant cohort with no histopathologic evidence of EED (Aim IA). Furthermore, we will perform an intervention study (Aim IB). The undernourished non-pregnant cohort will be randomized into two groups (n=30/arm) and receive daily dietary supplementation with either shelf-stable microbiota-directed balanced energy protein (MD-BEP) or ready-to -use supplementary food balanced energy protein (RUSF-BEP) for 90 days. After cessation of the intervention they will be further followed up for another 270 days and biological samples will be collected at scheduled time points. The well-nourished non-pregnant cohort will not receive any nutritional intervention will serve as a reference control group. The undernourished pregnant cohort will also be randomly (n=30/arm) assigned to receive either MD-BEP or RUSF-BEP daily for 6 months until the child birth and thereafter for 3 months and followed up for another 9 months. During this period anthropometry will be measured and biological samples including fecal and plasma samples will be collected from the mothers and their infants in scheduled time points. Anthropometric, socio-demographic and laboratory assay data will be compared between the groups and candidate EED biomarkers will be correlated with nutritional status, histological analyses and score of EED, plus assessments of microbial community structure will be examined.

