### Anthropometry and body composition

Nutritional status will be assessed through anthropometry. Body weight and BMI will be determined at the anthropometry timepoints mentioned in Figs. 2 and 3. Bioelectric Impedance Analysis (BIA) will be used to measure total fat and fat-free mass before, during and after the intervention.

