### Follow-up of pregnant women

Pregnant women will be enrolled at the beginning of second trimester and followed up till one year after childbirth. For the undernourished pregnant women, antenatal care (ANC) services from nearby healthcare facilities will be ensured by study staff. Trained Health Workers (HWs) will visit the homes of all enrolled pregnant women once a month and will involve the family members, including mothers, mothers-in-law, and husbands, along with the pregnant women in the sessions according to the convenience and availability of the participant and her family members. The woman and her family will receive advice on the importance of adequate weight gain during pregnancy, additional energy requirements, and improving dietary diversity. The pregnant women will be advised to seek routine ANC according to the schedule and to regularly take micronutrients (iron, folic acid, and calcium) provided through routine ANC. On each visit, the participants’ dietary diversity and rate of weight gain will be evaluated, and they will be given instant feedback. The participants will have access to field offices where they shall receive a thorough physical check-up by a registered physician. If any unwanted event occurs during the follow-up period, the participants will be referred to the nearest maternal clinic or appropriate healthcare facility.

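### Percent change in weight and in BMI is one quantity, and comparing arms on an undefined probability of improvement would lose information at 30 per arm

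*Protocol article*

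**What the plan says.** The section *Modeling the changes in centiles of anthropometry curves* defines the derived variable: "Percentage changes in weight and BMI will be calculated by subtracting baseline values from follow-up measurements", with the difference divided by baseline and multiplied by 100. It then says "Generalized linear mixed-effects models (GLMMs) will be used to model the percent changes of indices". The next sentence changes the target: "GLMMs will estimate the probability of improvement in the BMI and weight in the intervention group from baseline", compared with the control group and adjusted for covariates. It gives no threshold for improvement and makes no exception for either cohort.

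The preceding section, *Modeling the clinical effectiveness of the intervention*, plans a linear mixed model for continuous outcomes, with treatment, baseline covariates and time trends as fixed effects, which "will be employed to assess the impact of the intervention on the outcomes described above". It does not name weight or BMI. Both are measured, under *Anthropometry and body composition*: "Body weight and BMI will be determined at the anthropometry timepoints mentioned in Figs. 2 and 3".

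The women are aged 18 to 35, and each undernourished cohort is randomised 30 per arm. For the pregnant cohort the time frame is: "Pregnant women will be enrolled at the beginning of second trimester and followed up till one year after childbirth". *Sample size calculation and outcome* says that no formal power calculation was done because the research is exploratory.

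**The concern.** There are three difficulties in one short section.

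- **Duplication.** Weight and BMI are treated as two indices, but their percent changes carry the same information. Printed side by side, two agreeing results could be taken as mutual support.
- **Two targets that do not match.** A model of percent change gives a difference in mean percent change. A probability of improvement needs a binary response. The only between-arm quantity that the section states is the second one. It discards the size of each woman's gain, and its cut is left open.
- **The pregnant cohort.** Baseline lies early in the second trimester and follow-up crosses delivery. Before delivery, nearly every woman in either arm may be above baseline because of the pregnancy. Across the whole period, one change from baseline mixes gestational gain, loss at delivery and postpartum weight.

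The stake is the precision and meaning of the anthropometric comparison in a trial whose numbers are small and already fixed.

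**Working it through.** The document states no power, effect size or SD, so there is no figure of its own to reproduce.

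**Inputs from the document.** 30 per arm in each randomised cohort; significance at 0.05 (two-sided assumed); ages 18 to 35; pregnant baseline at the start of the second trimester.

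**Assumptions.** Change is normally distributed. Improvement means any increase above baseline. The true arm difference is 0.73 SD, about what 30 per arm can detect with 80% power: (1.96 + 0.84) × √(2/30) = 0.72 SD. The control group is read as the RUSF-BEP arm, although the article also uses that term for the well-nourished women.

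**1. Identity.** BMI = W/h². With h constant, (W1/h² − W0/h²) / (W0/h²) = (W1 − W0)/W0. Illustration with assumed values: at 1.50 m, going from 40 to 42 kg takes BMI from 17.78 to 18.67, and both rise by 5.0%. In 60 simulated women the largest discrepancy was 1.7 × 10⁻¹⁴ percentage points, which is rounding. If height were re-measured at each visit with an assumed error of 0.3 cm, the correlation would still be about 0.99. After dichotomising at any increase with height fixed, the women who improve on weight are exactly those who improve on BMI.

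**2. Power, continuous versus binary.** Continuous: Φ(0.73 × √(30/2) − 1.96) = Φ(0.867) = 80.7%. Binary: with comparator mean change μ in SD units, p1 = Φ(μ) and p2 = Φ(μ + 0.73). Power is Φ{[(p2 − p1) − 1.96 √(2p̄(1−p̄)/30)] / √([p1(1−p1) + p2(1−p2)]/30)}, where p̄ is the mean of p1 and p2. Relative efficiency is φ(μ)²/[p1(1−p1)].

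| μ (SD) | p1 | p2 | Binary power | Fisher exact | Relative efficiency | n/arm for 80%, binary |
|---|---|---|---|---|---|---|
| 0 | 50.0% | 76.7% | 57.8% | 47% | 0.64 | 50 |
| 0.5 | 69.1% | 89.1% | 47.4% | 36% | 0.58 | 65 |
| 1 | 84.1% | 95.8% | 32.2% | 14% | 0.44 | 103 |
| 2 | 97.7% | 99.7% | 9.8% | <1% | 0.13 | 523 |

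The continuous analysis needs 30 per arm for 80% power in every row.

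**3. Pregnant cohort, up to delivery.** For assumed gains of 5 to 9 kg with SD 2.5 to 3.5 kg, P(any increase) = Φ(mean/SD). This runs from Φ(5/3.5) = 92.3% to Φ(9/2.5) = 99.98%. Binary power for 0.73 SD is then 20% down to 3%.

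**4. Pregnant cohort, after delivery.** For an assumed retained gain of 0 to 3 kg with SD 3 kg, between Φ(0) = 50% and Φ(1) = 84% of women are above baseline, so the ceiling need not hold.

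**5. Sensitivity to the cut.** Take an assumed gestational gain of 12% with SD 6%. A cut at zero is the μ = 2 row: 9.8% power. A cut at 10% gives p1 = Φ(2/6) = 63.1% and p2 = Φ(0.333 + 0.73) = 85.6%. The same formula gives Φ[(0.226 − 0.221)/0.109], or about 52%. That is well above 9.8% and still below 80.7%.

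**The case against.** A reader might infer that weight and BMI are reduced to a binary outcome and nothing else. The document does not support that. The same section says that the percent changes themselves are modelled, and the linear mixed model section covers continuous outcomes with baseline covariates and refers back to outcomes described earlier, where weight and BMI appear. On that reading a continuous analysis is already planned, and power is lost only if the probability leads. This stands. What remains is that the centiles section is the only analysis text that names the two measures, and its stated between-arm quantity is the probability.

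A reader might also infer that the endpoint cannot separate the arms in pregnant women. That is too strong. The cut at zero is an assumption, since improvement is undefined; a higher cut recovers part of the power (step 5), and the ceiling need not persist postpartum (step 4). A responder definition may also sit in a fuller document not shown.

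It is fair, too, that every mean and SD above is assumed, that the calculations use a single time point where the plan has adjusted repeated-measures models, and that no power target exists to be missed. The loss is therefore relative.

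Finally, nothing presents weight and BMI as independent or co-primary. Reporting both is redundant, not invalid, and the risk of apparent corroboration concerns how results would be read. None of this removes the identity of the two percent changes or the mismatch between the two modelling sentences.

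**Conclusion.** The point holds in a limited form, at moderate severity.

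- **Certain, with no outside figure:** at fixed adult height the two percent changes are one quantity, and a probability of improvement is not what a model of continuous percent change delivers.
- **Conditional on the probability being the arm comparison with a cut at any increase:** relative efficiency is at best 0.64, and the fall in power is that in step 2, from about 81% to between 58% and 10%. The direction is the same in every scenario tried; the size depends on the assumed effect and comparator change.
- **Conditional on assumed gestational gains and the same cut:** the measure is nearly uninformative until delivery. Whatever the cut, a single change from baseline across delivery mixes different processes.

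It is not a critical defect. The goals under *Hypothesis and objectives* concern microbiota mechanisms, surrogate biomarkers and EED rather than weight or BMI, and the study is declared exploratory.

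**What to change.** Rewrite the centiles section, before the outcome data are analysed, to say the following:

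- One measure, weight or BMI, is the anthropometric outcome for the between-arm comparison. It is analysed as a continuous value in the linear mixed model already specified, with its own baseline value as covariate, and the arm difference is reported with a 95% confidence interval (in kg if weight is chosen).
- In the pregnant cohort, antenatal weight, accounting for gestational age at measurement, and postpartum weight are analysed separately.
- Any proportion improved is a secondary description with a threshold stated in advance.
- Percent change in weight and in BMI are not presented as two separate results.

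The cost is a change of wording; measurements, visits and sample size stay as they are. The one loss is that the easily communicated proportion improved moves to a secondary place.
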